**Protocol Title:** Vitamin D supplementation: Impact on severe pneumonia among under-five children

| Project Summary |
| --- |
| Principal Investigator: [name] |
| Research Protocol Title: Vitamin D supplementation: Impact on severe pneumonia among under-five children |
| **Background:**   1. Burden: Pneumonia is the leading cause of morbidity and mortality in under-five children, particularly in developing countries. 2. Knowledge gap: Although many studies have reported an association between vitamin D deficiency and pneumonia, there is lack in information on its therapeutic impact, i.e. the impact of vitamin D supplementation in the management of childhood pneumonia. 3. Relevance: Vitamin D plays an important role in modulating the innate immune response against infections. We, therefore, propose to conduct this study to assess the impact of vitamin D supplementation, in addition to standard antibiotic and supportive therapy, on the outcome of severe childhood pneumonia.   **Hypothesis**: We hypothesise that in the management of hospitalized severe pneumonia in under-five children, vitamin D3 supplementation, as an adjunct to the standard antibiotic and other supportive therapy, will hasten recover from severe pneumonia and may thereby shorten duration of severe pneumonia and also reduce the risk of new episode of pneumonia.  **Objectives:** The objective of our study is to assess the clinical benefit of oral supplementation of vitamin D3, in addition to standard antibiotic and other supportive therapy, to hospitalised, under-five children with severe pneumonia.  **Methods:** This would be a randomised, double blind, controlled clinical trial (RCT). Children of either sex, aged 3-59 months, attending the Dhaka Hospital of icddr,b, with clinically diagnosed severe pneumonia will comprise the study population. Eligible children will be allotted a sequential study number, which will have been previously assigned to vitamin D or placebo in accordance with the randomisation. The study staff and mothers/ caregivers of the children will be blinded as to whether vitamin D3 or placebo has been added to their child's diet. Infants aged 3-5 months will receive breast milk and/or infant formula, and those 6 months or older will receive “Milk Suji” as a complementary food. Vitamin D3 supplementation will be given on five consecutive days, from the day of enrolment in addition to standard antibiotic and other supportive therapy.  **Outcome measures/variables:**  Primary outcome measure will be time to resolution of severe pneumonia.  Secondary outcome measures will be duration of hospitalization, fever, tachypnoea, chest in drawing, hypoxia, lethargy and inability to feed during hospital stay and as well as new episode of pneumonia after discharge. |

#

**Description of the Research Project**

##

## Hypothesis to be tested:

| In a hypothesis testing research proposal, briefly mention the hypothesis to be tested and provide the scientific basis of the hypothesis, critically examining the observations leading to the formulation of the hypothesis. |
| --- |

Does this research proposal involve testing of hypothesis:  No  Yes (describe below)

We hypothesise that supplementation of vitamin D3 (Cholecalciferol), in addition to standard antibiotic and other supportive therapy in the management of under-five children with severe pneumonia will significantly shorten the duration of severity of pneumonia and thereby reduce hospital stay and also reduce the risk of new episode of pneumonia.

## Specific Objectives:

| Describe the specific objectives of the proposed study. State the specific parameters, gender aspects, biological functions, rates, and processes that will be assessed by specific methods. |
| --- |

**Objective:** To assess the clinical benefit of oral vitamin D3 supplementation, in addition to standard antibiotic and other supportive therapy, in the management of hospitalised, under-five children with severe pneumonia.

**Primary objective:** To compare the duration of severe pneumonia of children in the two study groups receiving the standard therapy (appropriate antibiotic and other supportive therapy) with those receiving vitamin D supplementation in addition to the standard therapy.

**Secondary objectives:**

- To compare the duration of hospitalization, fever, tachypnoea, chest in drawing, hypoxia, lethargy and inability to feed during hospital stay, in under-five children in the two study groups, as mentioned under the primary aim.
- To compare the recurrence of new episode of pneumonia over the next 6 months after discharge from hospital in the two study groups.
- To identify the optimum safety dose of vitamin D3 for different groups of under-five children.
- In severe pneumonia patient who also have acute watery diarrhoea we will assess the indirect absorption of vitamin D by measuring serum vitamin D level and will also assess the clinical outcome in the subgroup.

## Background of the Project including Preliminary Observations:

| Provide scientific validity of the hypothesis based on background information of the proposed study and discuss previous works on the research topic, including information on sex, gender and diversity (ethnicity, SES) by citing specific references. Critically analyze available knowledge and discuss the questions and gaps in the knowledge that need to be filled to achieve the proposed aims. If there is no sufficient information on the subject, indicate the need to develop new knowledge. |
| --- |

##

Pneumonia is the leading cause of morbidity and mortality in under-five children, particularly those living in developing countries.1,2 In 2010 there were 120 million episodes of pneumonia in children younger than five years and 14 million of pneumonia cases progress to severe and life-threatening condition requiring urgent hospital care.3 In 2011 it was estimated that 1.3 million pneumonia led to death worldwide.3 In Bangladesh, pneumonia remains as a significant health problem and is one of the major causes of childhood mortality.4 The Millennium Development Goal 4 (MDG4) aims to reduce child mortality by two thirds (2/3rds) by the year 2015. The success of achieving the target depends on reducing the prevalence of pneumonia in children along with efficient management of pneumonic children.

Many research studies have been conducted to identify effective interventions to reduce global burden of deaths due to pneumonia. They mostly focused on preventive strategies such as improving nutritional status and exclusive breast-feeding, reducing indoor air-pollution and overcrowding, improving access to effective antibiotics, care-seeking behaviour, referral practices and quality of case management.5  There is increasing recognition that nutritional deficiencies, including that of micronutrients, play an important role in infectious diseases, such as pneumonia and their outcome.6  Identifying an effective nutritional intervention, including micronutrients to reduce morbidity and shorten hospitalisation, would improve medical care and morbidity.7 Many trials have investigated the benefits of vitamin A supplements; however, with the exception of reduction in measles associated deaths and overall mortality, no significant reduction of morbidity and mortality from acute lower respiratory tract infections (ALRI) was observed.8 Zinc supplementation has been reported to reduce ALRI incidence by 41%, and has also been reported to accelerate recovery from pneumonia when used as an adjunct to effective antibiotic therapy; however, another study in India reported negative outcomes.9-11

Vitamin D plays a crucial role in calcium and phosphorus homeostasis, and is a key factor in skeletal mineralization. Its deficiency causes rickets and impaired skeletal growth in children and osteomalacia in adults.12 Clinical and subclinical vitamin D deficiency in children has been reported to be a significant risk factor for severe ALRI.13 In addition to maintenance of calcium levels, Vitamin D also plays an important role in modulating the innate immune response against infections.14

It has been reported that 1,25 dihydroxyvitamin D3, the active metabolite of vitamin D, is important for promoting and regulating immune responses in vitro,which is also supported by other studies in human.12,15-17 Scientists at the University of **Copenhagen have discovered that** when a T cell is exposed to a foreign pathogen, a signaling device or 'antenna', known as a vitamin D receptor, is extended, and it searches for vitamin D with it. This means that the T cell activation will cease without vitamin D. T cell won't even begin to mobilise if they cannot find enough vitamin D in the blood. Successfully activated T cells transform into one of two types of immune cells- they may either become killer cells that attack and destroy all cells carrying traces of foreign pathogen or may become helper for T cells to detect and kill foreign pathogens such as clumps of bacteria or viruses. T cells rely on vitamin D for their activation and they would remain dormant, ‘naïve’ to the possibility of threat if vitamin D was lacking in the blood.18

Research studies conducted thus far highlights the link between Vitamin D and pneumonia. For example, an Indian study reported subclinical vitamin D deficiency as a significant risk factor for severe ALRI in under-five children.12 An Ethiopian study reported clinical signs of rickets in 41% of 300 consecutive under-five children attending the outpatient ward; in the inpatient case control study rickets was associated with 13-fold higher risk of pneumonia.19 Another study in Yemen reported significant association between rickets and the treatment outcomes from very severe pneumonia.20 In Iran, 43% of 200 children with rickets had radiological pneumonia, and in Kuwait pneumonia was diagnosed in 44% of 250 children with Vitamin D deficiency rickets.21,22 A study identified 131patients between 1979 to 1988, and compared two age matched and sex matched groups- one with rickets and the other group of healthy controls without rickets. The study observed pneumonia to be more common in rachitic patients than in the controls.23 A hospital-based, case control study in Egypt reported ARI in 81% of children with rickets compared to 58% in the controls.24 A systematic review and meta-analysis of randomized controlled trials on vitamin D and respiratory tract infections reported that vitamin D has a protective effect against respiratory tract infections and dosing once daily seems most effective than bolus dose.25

A hospital-based, randomised, controlled trial in Kabul shows that supplementation of a bolus dose of 100,000 IU vitamin D in addition to antibiotic to young children with pneumonia was associated with reduced repeat episode of pneumonia, without reducing the hospital stay.26 Another study in India reported no beneficial effect of small consecutive dose of vitamin D with antibiotics on resolution of severe pneumonia among under five children.27

However limited information is available in Bangladesh about the vitamin D status in children. A survey conducted at Dhaka neighborhood found that among 319 children between the age group of 16 to 20 months and 164 children between the age group of 30-36 months respectively 51% and 43% had blood vitamin D (25-OH-D) level below the cut off value (47.7 nmol/L) of 25-OH-D (Personal communication from [name], unpublished). From the data on National Rickets Survey in Bangladesh in 2008, it was documented that 98% children were vitamin D deficient out of 154 rachitic children (Personal communication from Dr. [name], unpublished) and a study from Chakaria observed that 2 (20%) children out of 10 rachitic children were vitamin D deficient.28 A matched case-control study in North-Eastern part of Bangladesh noted a relationship between Vitamin D status and early childhood ALRI, and young age group was the only risk factor for vitamin D deficiency.29

Although many studies have shown the association between vitamin D deficiency and pneumonia, there is limited information on the effect of vitamin D supplementation in the outcome of children with pneumonia.12, 19-27 We are, therefore, interested to conduct a randomised, controlled clinical trial to assess the impact of vitamin D supplementation, in addition to standard antibiotic therapy, on the duration of hospitalization, as well as on the duration of severe pneumonia of the affected children and further new episode of pneumonia.

Moreover co-morbidity of pneumonia and diarrhea is a burning public health problems accounting more than one third of 7.6 million global childhoods under five deaths30,31 and evaluation of the role of vitamin D in such population may have great value.

## Research Design and Methods

| Describe the research design and methods and procedures to be used in achieving the specific aims of the research project. If applicable, mention the type of personal protective equipment (PPE), use of aerosol confinement, and the need for the use BSL2 or BSL3 laboratory for different part of the intended research in the methods.. Define the study population with inclusion and exclusion criteria, the sampling design, list the important outcome and exposure variables, describe the data collection methods/tools, and include any follow-up plans if applicable. Justify the scientific validity of the methodological approach (biomedical, social, gender, or environmental).  Also, discuss the limitations and difficulties of the proposed procedures and sufficiently justify the use of them. |
| --- |

**Study site:**

The study will be conducted at the Dhaka Hospital of the International Centre for Diarrhoeal Disease Research, Bangladesh (icddr,b), Dhaka, Bangladesh. This hospital has separate ward for management of children with severe pneumonia and also has an Intensive Care Unit (ICU), equipped with mechanical ventilator, cardiac monitors, and other supportive facilities for management of critically ill patients.

**Study population:**

Children of either sex, aged 3-59 months, attending the Dhaka Hospital of icddr,b, Dhaka with clinically diagnosed severe pneumonia (case definition described in a later section) will comprise the study population.

**Study design:** This would be a randomised, double blind, controlled clinical trial (RCT).

**Inclusion criteria:**

Children of either sex aged 3 - 59 months, with a clinical diagnosis of severe pneumonia with or without diarrhea.

**Exclusion criteria**

1. Known case of hypercalcaemia or allergy to vitamin D, as determined by history or previous medical records.
2. Congenital Heart disease, evidenced by clinical exam or past medical records.
3. Renal or hepatic insufficiency, evidenced by clinical exams or past medical records.
4. Known case of tuberculosis, evidenced by medical records
5. Known case of asthma, evidenced by history and clinical exam findings.
6. Critically ill children requiring ICU care, such as those with septic shock or cardiac arrest or apnoea.
7. Received vitamin D or calcium supplementation within the last 4 weeks before current admission, as evidenced by history or medical prescription.
8. Baseline ionized calcium level above the normal limit for the main phase of the study.

**Study Intervention**

Eligible children satisfying all the study criteria will be randomized, in equal numbers to receive the vitamin D3 supplementation or placebo in their diet in addition to the standard therapy (appropriate antibiotic and supportive therapy). Infants aged 3-5 months will receive breast milk and/or infant formula, and those 6 months or older will receive complementary food such as “Milk Suji”. Vitamin D3 or placebo will be administered adding with their diet. For exclusively breast fed babies vitamin D3/placebo will be administered in expressed breast milk.

We will decide the dose of vitamin D3 supplement for this study after piloting. Two studies have evaluated the impact of vitamin D3 in childhood pneumonia; one in Kabul with a bolus dose of vitamin D3 (100,000 IU) 26 and another study in India with small dose (1000/2000IU) 27 of vitamin D3 on 5 consecutive days.  Both the studies have shown no effect of vitamin D3 in hospitalized pneumonia children but the study in Kabul showed vitamin D3 supplementation could reduce the occurrence of new episode of pneumonia. There was a critical review of the second study in India which recommended use of 10,000 IU vitamin D3 on 5 consecutive days.32 These two studies have not done serum 25(OH)D and calcium level assay and did not find any symptoms of vitamin D toxicity or adverse effect. Although researchers first identified the fat-soluble vitamin cholecalciferol almost a century ago and studies have now largely elucidated the transcriptional mechanism of action of its hormonal form,1_,25-dihydroxyvitamin D3 [1_,25(OH)2D3], we know surprisingly little about mechanisms of vitamin D toxicity.33 In spite of current data support the viewpoint that the biomarker plasma 25(OH)D concentration must rise above 750 nmol/L to produce vitamin D toxicity, the more prudent upper limit of 250 nmol/L might be retained to ensure a wide safety margin.33,34 Therefore for this study to ensure the safe dose of vitamin D3 for the children we will first proceed through piloting.

For piloting we will enroll 20 patients and group them into two that is ten patients in each group. We will intervene one group with vitamin D3 supplement 10,000 IU for five consecutive days. Another group will receive stratified dose of vitamin D3 according to age. That is 20,000IU vitamin D3 in children <6 months, 50,000 IU in children 6-12 months and 100,000 IU in children 13-59 months of age on first day and thereafter 10,000 IU for next 4 days. We will observe any adverse event after the intervention and monitor the serum 25(OH)D level on admission, at discharge (day 5) and after two weeks of discharge as the half life of vitamin D3 is two weeks. To collect blood sample after two weeks of discharge parent/guardian will be requested for follow up visit at hospital with the child at that time. In case of failure to visit the hospital study staff will visit their home for follow up of the child and collection of blood sample for serum 25(OH)D level assay. We will also monitor serum calcium level on day of admission, 2nd day and at discharge for safety monitoring as vitamin Ds primary roll is to control the levels of calcium in the body by constantly adding calcium to or taking calcium from bones. Depending on the adverse event and serum 25 (OH)D and calcium level of this pilot phase, we will decide the final dose for vitamin D3 intervention for the study. We will consider the toxic level of 25(OH)D as 250nmol/L33,34 and the upper limit of the serum calcium would be 2.63 mmol/L for safety monitoring.35 If we find serum 25(OH)D and calcium level on admission above this level we will stop further intervention. After finalization of dose in this study we will assay the 25(OH)D and calcium level on admission and on 5th day or earlier at discharge.

For the study, participants will be randomly assigned to one of two masked parallel intervention groups, with allocation concealment: vitamin D3 (cholecalciferol) or matched placebo. The vitamin D3 will be a high- concentration (20,000 IU D3 per mL) liquid formulation (Vigantol Oil, Merck KGaA, Germany), and the placebo will be miglyol oil 812 (Sasol, Germany), the vehicle used in Vigantol Oil. These active supplement and selected placebo are identical in appearance and both are tasteless. We have added vigantol oil and miglyol oil in 50 ml of “Milk Suji”, infant formula and expressed breast milk and there was no difference in appearance, color, odor or taste of diets with Vigantol oil (vitamin D3) or miglyol oil (placebo).

The allocated intervention, vitamin D3/placebo will be administered by adding in the diets within two hours of the first dose of parenteral antibiotics on the day of admission after confirming baseline ionized calcium within normal range and in the first morning diet for days 2-5 of the hospitalisation. Children who are unable to take oral diet, in that case vitamin D3/placebo will be administered through nasogastric tube with their diet. Intervention will be repeated if the child has vomiting within 30 minutes of intervention.

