**Vitamin D dosing for the main phase of then study:**

Based on the findings from the pilot phase of the study we have received IRB approval for the optimal safe dose of vitamin D where patient will receive stratified dose of vitamin D3 according to age. That is 20,000IU vitamin D3 in children <6 months, 50,000 IU in children 6-12 months and 100,000 IU in children 13-59 months of age on first day and thereafter 10,000 IU for next 4 days.

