**Randomisation and Allocation Concealment**

The eligible children will be allotted a sequential study number, which will have been previously assigned to vitamin D3 or placebo in accordance with the randomisation. A computer generated random list will be developed by a person not involved in the study in any way. Participants and the research staff will be blinded to allocation. Pharmaceuticals Company will prepare the supplements off-site using individual opaque glass vials labeled with concealed unique identifiers for vitamin D3 and placebo. Allocation concealment will be done by sealed envelope and will be kept in a secured place by the person not associated with the study in any way; the envelope will be opened at the end of the study only, prior to data analysis.

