**Monitor ionized calcium level instead of total serum calcium:**

We will do blood test for serum ionized calcium instead of total serum calcium for the main phase of the study. In our pilot phase of the study we have found about 50% of our enrolled children with severe pneumonia were severely malnourished. These children may have low albumin level and so may not reflect the actual calcium status of the body through total serum calcium. Moreover ionized calcium gives more accurate picture of calcium in blood comparing to total serum calcium.

In that case as we have considered the upper normal limit of total serum calcium for safety monitoring, in case of ionized calcium the upper limit (normal range: 1.15-1.33 mmol/L)38 will be considered for safety monitoring. So the child having ionized calcium above 1.33mmol/L on admission will be stopped from having further intervention and excluded from the study.

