## Sample Size Calculation and Outcome (Primary and Secondary) Variable(s)

| Clearly mention your assumptions. List the power and precision desired. Describe the optimal conditions to attain the sample size. Justify the sample size that is deemed sufficient to achieve the specific aims. |
| --- |

From the patients records who were admitted to the Matlab Hospital of icddr,b and calculated duration of severe pneumonia (mean=6 , standard deviation=2.5)10. To calculate sample size corresponding to the hypothesis that the Vitamin D supplement will reduce duration of severe pneumonia we assume the following things:

Mean duration in control group m1=6 days

Standard deviation in control group s1=2.5

Mean in Vitamin D group m2= a sequence of duration up to 5 for example, mean duration in this group is 1 or 2 or 3 or 4 or 5 days.

Standard deviation in Vitamin D group s2 = s1=2.5

Probability of Type-I error alpha= 0.05

Power = 90%

The Mathematical formula is for each group

[figure not shown]

Where
[figure not shown]
 and
[figure not shown]
are standard normal deviate at 5% (alpha) and 10% (beta),
[figure not shown]
 is the common variance in this case this is equal to
[figure not shown]
 and
[figure not shown]
 is the squared difference between duration in both groups. Putting all the values we have

[figure not shown]

With above assumption we calculated as series of sample size and then consider 30% dropout in each case we adjust the calculated sample size. The following table gives the result of the sample size calculation.

| Mean in Duration in control group | Mean duration in Vitamin D group | Effect Size  in percentage | Standard deviation is both group | Initial sample size  in each group | Sample size after adjusting 30% dropout |
| --- | --- | --- | --- | --- | --- |
| 6 | 5 | 16.7 | 2.5 | 108 | 155 |
| 6 | 4 | 33.3 | 2.5 | 28 | 40 |
| 6 | 3 | 50.0 | 2.5 | 13 | 19 |
| 6 | 2 | 66.7 | 2.5 | 8 | 12 |
| 6 | 1 | 83.3 | 2.5 | 6 | 9 |

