## In this study we will see the impact of vitamin D on severe pneumonia among under five children. Although researchers first identified the fat-soluble vitamin D (cholecalciferol) almost a century ago, we know a little about mechanisms of vitamin D toxicity. Even with current data support the viewpoint that the biomarker plasma 25(OH)D concentration must rise above 750 nmol/L to produce vitamin D toxicity, the more prudent upper limit of 250 nmol/L might be retained to ensure a wide safety margin. Therefore for this study to ensure the safe dose of vitamin D3 for the children we will first proceed through piloting. We will observe any adverse event after the intervention and monitor the serum 25(OH)D level on admission, at discharge (day 5) and after two weeks of discharge as the half life of vitamin D3 is two weeks. We will also do serum calcium level on day of admission, 2nd day and at discharge for safety monitoring as vitamin Ds primary roll is to control the levels of calcium in the body by constantly adding calcium to or taking calcium from bones. Depending on the findings of this pilot phase, we will decide the final dose for vitamin D3 intervention for the study. We will consider the toxic level of 25(OH)D as 250nmol/L33,34 and the upper limit of the serum calcium would be 2.63 mmol/L for safety monitoring.35 If we find serum 25(OH)D and calcium level on admission above this level we will stop further intervention.

For the main phase of the study we will do serum test for ionized calcium instead of total calcium.

As we have considered the upper normal limit of total serum calcium for safety monitoring, in case of ionized calcium the upper limit (normal range: 1.15-1.33 mmol/L) will be considered for safety monitoring. So the child having ionized calcium above 1.33mmol/L on admission will be stopped from having further intervention and excluded from the study.

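### The admission-day dose is tied to a two-sided ionised calcium range, while the exclusion and safety rules set only an upper limit

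*Protocol*

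**What the plan says.** The protocol states a calcium rule for the main phase in several places.

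- **Dosing (Study Intervention).** The allocated product is given within two hours of the first parenteral antibiotic on the day of admission, "after confirming baseline ionized calcium within normal range and in the first morning diet for days 2-5 of the hospitalisation".
- **Eligibility (Exclusion criteria, item 8).** The child is excluded for "Baseline ionized calcium level above the normal limit for the main phase of the study".
- **Safety limit.** The section on monitoring ionised instead of total calcium, and the safety text under Ethical Assurance, both say that "in case of ionized calcium the upper limit (normal range: 1.15-1.33 mmol/L) will be considered for safety monitoring". Both then stop and exclude only a child above 1.33 mmol/L on admission.
- **Hospital monitoring (Monitoring during hospital stay).** Action follows when calcium is above the safety level or hypercalcaemia develops. Nothing is said about low values.

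Study Intervention adds that "Eligible children satisfying all the study criteria will be randomized", and Randomisation and Allocation Concealment that "The eligible children will be allotted a sequential study number". Data Analysis specifies intention-to-treat analysis. The main-phase regimen is age-stratified: 20,000 IU under 6 months, 50,000 IU at 6-12 months and "100,000 IU in children 13-59 months of age on first day and thereafter 10,000 IU for next 4 days". The four later daily doses are 10,000 IU in every age group.

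**The concern.** The dosing condition has two bounds and every other calcium rule has one. A child at, say, 1.10 mmol/L passes criterion 8, is randomised and counts in the analysis, but does not satisfy the stated condition for the first dose. No section says what to do with that child. Staff could dose, delay beyond the two-hour window, omit the dose or treat the child as ineligible.

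The condition governs the loading dose, the largest of the five. A child in the vitamin D arm who misses it is analysed as treated after much less than the planned amount. A placebo child who misses it loses nothing active. The contrast between arms would shrink. An analysis plan cannot repair this, because it cannot restore a dose that was not given.

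**Working it through.** **1. The rules side by side**

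| Protocol section | Acts above 1.33 mmol/L | Acts below 1.15 mmol/L |
|---|---|---|
| Exclusion criteria, item 8 | Yes (above the normal limit) | No |
| Monitor ionized calcium level | Yes | No |
| Monitoring during hospital stay | Yes (above the safety level) | No |
| Safety text under Ethical Assurance | Yes | No |
| Study Intervention, day 1 | Yes | Yes, if read literally |
| Study Intervention, days 2-5 | No calcium condition stated | No calcium condition stated |

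Study Intervention does not define the normal range itself. The only range the protocol gives for ionised calcium is 1.15-1.33 mmol/L, so that is the range used here.

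**2. Share of the course carried by day 1**

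Inputs are the main-phase doses. Formula: L = day-1 dose / (day-1 dose + 4 × 10,000 IU).

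- Under 6 months: 20,000 / 60,000 = 33.3%
- 6-12 months: 50,000 / 90,000 = 55.6%
- 13-59 months: 100,000 / 140,000 = 71.4%

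A vitamin D child who misses day 1 and receives days 2-5 gets 40,000 IU in every age group.

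**3. Illustration of the dilution, on assumed inputs**

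The protocol's planning row is "6 | 5 | 16.7 | 2.5 | 108 | 155": control mean 6 days, vitamin D mean 5 days, SD 2.5, 108 per group, 155 after 30% dropout. It reproduces with z-values 1.645 and 1.282:

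- 2 × (1.645 + 1.282)² × 2.5² / 1² = 107.05, rounded up to 108
- 108 / 0.70 = 154.3, rounded up to 155

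Power at 108 per group on the same basis is Φ[1 / (2.5 × √(2/108)) − 1.645] = 90.2%.

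Let f be the share of children below 1.15 mmol/L. The documents do not give f. Assume also that benefit is proportional to dose and that every such child loses day 1 and nothing else. The mean effect becomes 1 − f × L days, and power becomes Φ[(1 − fL) / (2.5 × √(2/108)) − 1.645].

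| Assumed f | Effect (days), L = 33.3% to 71.4% | Power |
|---|---|---|
| 0 | 1.00 | 90.2% |
| 5% | 0.98 to 0.96 | 89.4% to 88.3% |
| 10% | 0.97 to 0.93 | 88.4% to 86.1% |
| 20% | 0.93 to 0.86 | 86.4% to 80.9% |

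The lower end of each range puts every affected child in the oldest age group. With z = 1.960 in place of 1.645, power at 108 per group starts at 83.6%, and f = 10% gives 81.1% to 77.9%. The table shows how the effect would scale. It is not an estimate for this trial.

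**The case against.** The strongest reply is that the protocol already answers the question. The section devoted to main-phase calcium monitoring says that the upper limit is the one used for safety and attaches a consequence only to values above it. The exclusion criterion, the hospital monitoring text and the ethics text all agree. On that reading the phrase in Study Intervention is shorthand for a calcium that is not high, placed in a sentence mainly about timing. The protocol offers no reason to keep vitamin D from a child with low calcium. Most of this stands: the lower bound is probably unintended. It does not remove the conflict, because the instruction that staff dose from still carries both bounds.

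Four stronger readings are tempting, and the documents do not support them.

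- A reader might infer that the protocol orders the day-1 dose to be withheld below 1.15 mmol/L. It does not say so. That follows only from reading the condition literally.
- A reader might infer that all five doses are lost. The condition is attached to the admission dose alone, and the days 2-5 doses have none.
- A reader might treat the power table as a forecast. The share of low values, the proportional benefit and the literal compliance are all assumed.
- A reader might see a wider fault in the order of enrolment, blood draw and randomisation, or in the wording about stopping *further* intervention in a child not yet dosed. The eligibility, randomisation and dosing sections taken together put the calcium result before the study number and the first dose, so these are matters of clarity only.

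**Conclusion.** The inconsistency is real and minor. As worded, an eligible and randomised child below 1.15 mmol/L fails the condition for a dose worth 33%, 56% or 71% of the course, depending on age, and remains in the intention-to-treat comparison.

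If staff followed the wording, the estimated effect would be pulled towards zero. Neither arm would be favoured, because the condition rests on a baseline value and is applied blind to allocation. The size cannot be determined from the documents. On the assumptions above, power falls by about 1 to 4 percentage points if 5-10% of children are low. It approaches 81% only if 20% are low and all of those are aged 13-59 months. If staff already read the phrase as *not high*, nothing is lost.

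**What to change.** In Study Intervention, replace *within normal range* with *not above 1.33 mmol/L*, so that the dosing condition matches criterion 8 and the safety limit. A child below 1.15 mmol/L in the vitamin D arm would then receive the full allocated course of 60,000, 90,000 or 140,000 IU by age group.

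If the investigators do want a lower limit, put it in criterion 8, so that such children are excluded before randomisation and not left under-dosed after it.

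The cost is one phrase. No new test or visit is needed, because the calcium result is already required before the first dose.
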